## **2.5 Randomization and blinding**

Eligible subjects will be randomly assigned to the intervention group or control group in a ratio of 1:1. The randomization number sequence will be generated with R software by an independent statistician. Randomization number sequence will be stored by a non-involved investigator. The design is open label, but the outcome assessors and statisticians who are blinded to group allocation will be responsible for collecting and analyzing the data, respectively.

## **2.6 Interventions**

### **2.6.1 Control group**

The participants in the control group received routine postpartum care, including the observation of their vital signs (blood pressure, heart rate, respiratory rate, temperature and oxygen saturation of blood), the monitoring the amount of vaginal bleeding and discharge of lochia, the palpation of their fundus, cleansing of their vulva and an early interaction with their newborns.

### **2.6.2 Intervention group**

In addition to routine postpartum care, the participants in the intervention group were administered a 4-hour acupoint hot compress with a constant temperature of  $45\pm 2^{\circ}\text{C}$  within 30 minutes after delivery (Intervention I), 24 hours after delivery (Intervention II), and 48 hours after delivery (Intervention III).

As seen in Figure 3, for Intervention I, two hot cores (Model A) were administered on Shenque (RN8, in the center of the umbilicus) and Baliao (BL31-34, in the region of the sacrum, between the posterior-superior iliac spine and the posterior midline, in the 1st, 2nd, 3rd and 4th posterior sacral foramen, from the top to the bottom are Shangliao, Ciliao, Zhongliao, and Xialiao). Two hot cores (Model B) were bilaterally administered in Yongquan (KI1, on the sole, in the depression when the foot was in plantar flexion, and in the anterior depression when the foot was flexed, approximately at the junction of the anterior 1/3 and posterior 2/3 of the sole). During Interventions II and III, only one hot core (Model A) was administered on Shenque (RN8). The selection of acupoints is based on the clinical experiences of our hospital and the consultation with 10 experts in Chinese medicine. The location of the involved acupoints is described as per the Nomenclature and Location of Acupuncture Points (National Standard of People's Republic of China, 2006 [GB/T 12346-2006]).

[figure not shown]

**Figure 3. Acupoints**

(a) Shenque (RN8), in the center of the umbilicus;  
 (b) Baliao(BL31-34), in the region of the sacrum, between the postero-superior iliac spine and the posterior midline, in the 1st, 2nd, 3rd and 4th posterior sacral foramen, from top to bottom are Shangliao, Ciliao, Zhongliao, and Xialiao;  
 (c) Yongquan (KI1), on the sole, in the depression when the foot is in plantar flexion, and in the anterior depression when the foot is flexed, approximately at the junction of the anterior 1/3 and posterior 2/3 of the sole.

The hot compress was applied using a licensed Class II medical device, Hu-Chao-Nuan-Gong-Bao (produced by Jiangxi Shenghe Industrial Development Co., Ltd., Nanchang, China, with a license No. 20192090292). Four hot cores of Model A (11.5×8 cm with an entire patch of 13×10 cm) and another two hot cores of Model B (8×7 cm with an entire patch of 16×9 cm) were included in the licensed device. The material layer of a hot core consists of iron powder, water, activated carbon and inorganic salts, which are put into a sealed inner bag with a specific proportion. A specific water vapor transmission rate and a specific oxygen transmission rate of the air-permeable layer can keep a constant temperature (Figure 4).

[figure not shown]

**Figure 4. Structure diagram of hot core: From the outside to the inside are the non-woven fabric layer, air-permeable layer and heat conducting material layer**

## 2.7 Baseline data

Baseline information includes: Age; BMI(Prepregnancy); Race; ABO blood groups; Rh blood types; Place of residence; Educational level; Occupation category; History of tobacco consumption; History of alcohol intake; Insurance; Age of menarche; Menstrual cycle; Menstrual phase; Dysmenorrhea; Marital status; Couple relationship; Mode of conception; Prenatal care; Pregnancy complications; Fetus and appendages; Gestational age of delivery; BMI(Predelivery); Sleep duration per day; Trouble falling asleep; Appetite; Little interest or pleasure in doing things; Feeling down, depressed, or hopeless; Feeling nervous, anxious or on edge; Not being able to stop or control worrying; Labor induction; Augmentation by oxytocin; Rupture of membranes; Spinal analgesia for labor pain; Duration of labor stages; Perineum conditions; Assisted vaginal delivery; Placenta delivery method; Completeness of placenta; Fetal membranes; Curettage; Uterotonics drugs; Bowel movement during labor; Newborn weight; Newborn length; Apgar score; Time between birth and early sucking of newborns; Knowledge of breastfeeding; Postpartum diet within 28 hours after delivery; Postpartum diet during 52-76 hours after delivery; Postpartum appetite within 28 hours after delivery; Postpartum appetite during 28-52 hours after delivery; Postpartum appetite during 52-76 hours after delivery.

## 2.8 Outcomes measures

### 2.8.1 Primary outcome

The time point of the first urination after delivery and whether an indwelling catheter was used within 72 hours after delivery will be recorded. In the present trial, postpartum urinary retention is defined as the first urination occurring more than 6.5 hours after delivery and/or if an indwelling catheter is used within 72 hours after delivery.

### 2.8.2 Secondary outcomes

Postpartum uterine contraction pain: The visual analogue scale (VAS) will be used to evaluate the postpartum uterine contraction pain intensity: Using a horizontal ruler of 100 mm, “0” representing no pain and “100” representing unbearable pain. The pain VAS intensity will be respectively measured at  $6 \pm 0.5$  hours,  $28 \pm 0.5$  hours,  $52 \pm 0.5$  hours, and  $76 \pm 0.5$  hours after delivery.

Emotion symptoms: The Edinburgh Postnatal Depression Scale (EPDS) will be used for screening the depressive symptoms at  $76 \pm 0.5$  hours after delivery. It contains 10-item: pessimism, lack of interest, self-blame, worry, fear, impaired ability, sleep disorder, sadness, tearfulness, self-injury/suicidal ideation, each of which is scored from 0 to 3.

Lactation: The lactation initiation time will be recorded, and the breastfeeding milk volume, feeding mood and times, and the newborn weight will be measured at  $28 \pm 0.5$ ,  $52 \pm 0.5$ , and  $76 \pm 0.5$  hours after delivery, respectively. The breastfeeding milk volume is measured as “-” to “++++”: no milk outflow during finger extrusion(-); milk occasionally flows out during finger extrusion, which cannot meet the needs of the infants (+); milk flows out slowly when squeezed by fingers but does meet the needs of infants (+ +); milk continuously flows out during finger extrusion, which can meet the needs of infants (+ + +); there is milk flowing out in a jet shape when the nipple is squeezed by the fingers, which can meet the needs of infants (+ + + +).

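### The 28 h and 52 h assessment windows open half an hour before the 4-hour compress is due to end, with no rule that assessment follows patch removal

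*Supplement*

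**What the plan says.** **Treatment times.** Under protocol section 2.6.2, women in the intervention group "were administered a 4-hour acupoint hot compress with a constant temperature of" 45±2°C on three occasions. The first begins "within 30 minutes after delivery (Intervention I"). The others begin "24 hours after delivery (Intervention II), and 48 hours after delivery (Intervention III"). No tolerance is given for the second and third starts. The schedule in section 2.3.3 (Figure 1) shows the same times. On the placement of the patch at those two sessions: "During Interventions II and III, only one hot core (Model A) was administered on Shenque (RN8"), the umbilicus. The Model A patch measures 13×10 cm.

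**Assessment times.** Section 2.8.2 states: "The pain VAS intensity will be respectively measured at" 6±0.5, 28±0.5, 52±0.5 and 76±0.5 hours after delivery. The lactation items are taken at 28±0.5, 52±0.5 and 76±0.5 hours. "The breastfeeding milk volume is measured as" an ordinal grade from - to ++++, based on finger extrusion.

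**Blinding.** Section 2.5 describes the trial as open label, but adds that "the outcome assessors and statisticians who are blinded to group allocation will be responsible for collecting and analyzing the data", respectively. Under section 2.6.1 the control group receives routine care only, with no sham patch.

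**Analysis.** SAP section 6 fits the VAS with treatment, time and their interaction, and compares the arms at each time point by linear regression. Milk volume is modelled over time and compared at each time point by ordinal logistic regression.

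**The concern.** The centre of each of the two middle windows coincides with the nominal end of a compress. The first half of the window therefore lies inside the treatment period. Nothing in the protocol or SAP orders assessment after removal, requires the patch to be taken off or covered first, or says how assessor blinding is maintained at these visits.

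Two things are at stake, both for secondary outcomes.

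- **Milk-volume grade.** The grade depends on judgement: how freely milk flows, and whether it meets the infant's needs. Only the intervention arm ever has a patch, so an assessor who becomes aware of one knows the allocation. An assessor who knows the arm may grade differently, and an expectation of benefit would favour the compress.
- **Pain VAS.** Within one visit, some treated women may rate pain with heat applied and others after it has been removed. The difference between arms at 28 h and 52 h would then be an average over an unknown mixture of the two states.

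Pain relief and lactation are both named objectives in section 2.3.1, so these readings support stated claims of the trial.

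**Working it through.** The documents state no figure for this overlap, so there is none to reproduce first. The check is interval arithmetic on the documents' own times.

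**Inputs**
- Compress duration: 4 h (section 2.6.2).
- Starts: 0 to 0.5 h, 24 h and 48 h (section 2.6.2).
- Windows: stated time ±0.5 h, so 1.0 h wide (section 2.8.2).

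**Formulas**
- Compress end = start + 4 h.
- Share of window on compress = (compress end − window opening) / 1.0 h, limited to the range 0 to 1.

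**Results at the nominal times**

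| Visit | Compress on | Window | Overlap | Share of window |
|---|---|---|---|---|
| 6 h | from 0–0.5 h to 4.0–4.5 h | 5.5–6.5 h | none | 0% |
| 28 h | 24–28 h | 27.5–28.5 h | 28 − 27.5 = 0.5 h | 50% |
| 52 h | 48–52 h | 51.5–52.5 h | 52 − 51.5 = 0.5 h | 50% |
| 76 h | none (last ended at 52 h) | 75.5–76.5 h | none | 0% |

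At the 6 h visit the heat has been off for at least 5.5 − 4.5 = 1.0 h. At 76 h it has been off for about 76 − 52 = 24 h. The overlap therefore concerns 2 of 4 VAS time points and 2 of 3 milk-volume time points.

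**Sensitivity to the start time.** No tolerance is stated for the second and third starts, so these shifts are assumptions. For the 28 h window (the 52 h window behaves identically):

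| Start relative to 24 h | Compress ends | Share of 27.5–28.5 h on compress | Share of 28–29 h on compress |
|---|---|---|---|
| 0.5 h early | 27.5 h | 0% | 0% |
| 0.25 h early | 27.75 h | 25% | 0% |
| on time | 28.0 h | 50% | 0% |
| 0.25 h late | 28.25 h | 75% | 25% |
| 0.5 h late | 28.5 h | 100% | 50% |

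The last column applies the same formula to a window opening at 28 h. Moving the window removes the overlap for on-time and early starts. For late starts it only reduces it, so a condition that the patch is already off is needed as well.

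**What the analysis can and cannot separate.** The interaction term and the comparisons at each time point keep the 6 h and 76 h effects apart from those at 28 h and 52 h. Within the 28 h or 52 h visit, no variable for compress status is specified, so on-heat and off-heat readings are pooled.

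**The case against.** The strongest reply is that 28 = 24 + 4 and 52 = 48 + 4. The intended assessment is evidently at the end of the application, and ±0.5 h is an ordinary visit tolerance. Staff may in practice always remove the patch first. That is plausible, and it is why the overlap is a share of permitted time only. A reader might infer that about half of the intervention-arm readings are taken with heat on. The documents do not support that: they say nothing about how visits are spread within the window, and an early start would reduce the share just as a late one would raise it.

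Other stronger readings also go beyond the text.

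- **That blinding is broken.** The documents do not say the patch is visible. It lies on the umbilicus, clothing may cover it, and milk grading examines the breast. Section 2.8.2 does not say who performs the extrusion, and four of the five grades refer to the infant's needs, on which the mother's report could bear. That a blinded assessor assigns the grade is an inference from section 2.5. The text shows an unguarded risk to blinding and no more.
- **That the SAP treats the four VAS times as one undifferentiated series.** It does not: section 6 has a treatment-by-time interaction and a comparison at each time point.
- **That self-reported VAS and EPDS make the blinding statement false.** That question is separate from the window overlap. Section 2.5 openly calls the trial open label and claims no participant blinding, and the EPDS is taken only at 76 h, where there is no overlap.
- **That relief during heat is the wrong thing to measure.** The objective does not require lasting relief. The difficulty is an unrecorded mixture of states, whichever state the sponsor wishes to measure.

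What stands is the timing conflict itself and the absence of any rule that resolves it.

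**Conclusion.** The point holds as a timing conflict with a cheap remedy, limited to secondary outcomes at two visits. On the documents' own figures, 50% of each permitted window at 28 h and 52 h falls while the compress is due to be on. This rests on starts at exactly 24 h and 48 h and a full 4-hour application. With assumed start shifts of ±0.5 h the share ranges from 0% to 100%, and the share of actual readings cannot be known from the plan.

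The consequence for milk volume is a possible loss of assessor blinding at 2 of 3 time points. It depends on the assessor assigning the grade and becoming aware of the patch, neither of which is stated. The consequence for pain is a possible mixture of states at 2 of 4 time points, which the comparisons at each time point cannot resolve. No size of bias can be given. The primary outcome is not scheduled for these visits, and the 6 h and 76 h assessments are clear of any compress.

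**What to change.** Reconcile sections 2.5, 2.6.2 and 2.8.2 by changing the assessment rule and leaving the treatment times as they are.

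1. In both arms, replace the two middle windows with one-sided windows that open at the nominal end of the compress, for example 28 to 29 h and 52 to 53 h. Carry the change into Figure 1 and SAP section 6.
2. State that in the intervention arm the assessment follows removal of the patch, and say in section 2.5 how the assessor is kept unaware of allocation at these visits.
3. Add a CRF item recording whether a compress was in place at assessment.
4. Add to the SAP a sensitivity analysis of VAS and milk volume at 28 h and 52 h that excludes readings taken with a compress in place.

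If assessments have already been made, the windows can no longer be changed. The sensitivity analysis remains possible if application and assessment times were recorded, and the report can state the limit on assessor blinding at these visits.

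**Cost.** Revised window wording, one CRF item and one added analysis, with no extra visit. Assessments shift by up to half an hour. Someone other than the assessor may have to see that the patch is off beforehand, a small operational step. Readings will still fall soon after heat and women will still know their arm; the change makes the state at assessment uniform and protects the assessor's grade, and claims nothing beyond that.

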## 2.9 Safety Evaluation

The medical device for hot compress used in the present study is licensed by Medical Products Administration (Jiangxi Province, China) with a Licensed Number 20192090292. No adverse events (AEs) have been reported. In the present study, the safety evaluation will be comprehensively conducted and followed. In the study, the participants with sensory disorders have been excluded. Prior to obtaining consent from the participants, the potential AEs have been explained to the participants in detail. AEs will be monitored and recorded in detail throughout the whole study period.

#### **4. Risks**

In previous studies and clinical practice, acupoint hot compress used by Hu-Chao-Nuan-Gong-Bao has not been reported to have any adverse event.

If the subject experiences any adverse event, she can call the researcher at any time, and the researcher will fully explain and provide effective guidance. If an adverse event occurs, no matter it is related to this study or not, the subject will be treated in time. After confirmation by relevant experts from medical institutions and centers, the treatment costs will be covered by the clinical study sponsor and appropriate economic compensation will be given according to relevant national regulations.

#### **5. Benefits**

During the study, allocation to acupoint hot compress intervention group may reduce the incidence

of postpartum urinary retention, relieve postpartum uterine contraction pain, prevent emotional disorders, and promote lactation, which has a positive effect on puerperal health. Although there are evidences to suggest a satisfactory response, this does not guarantee a positive response for each subject. The intervention used in this study is not the only choice. If it is ineffective for the subject's condition, the subject can ask the physician for alternative treatment. During the study, if we learn of any information that may affect the continued participation of parturients in the study, the subject will be informed in time.

## **6. Data Management**

All the investigators will receive standard training and operate strictly according to the standard procedure. Double data entry will be applied to ensure the accuracy. A data monitoring committee will be set up before the first enrollment of participants. The original data will be collected and recorded in case report forms (CRFs). Each participant and the investigator will sign and record the date on CRFs, which will be maintained in a secure location. All the data and CRFs during the study are available from the corresponding author on reasonable requests. After publication of the study, all the relevant data will be stored for 3 years in Women's Hospital, School of Medicine, Zhejiang University.

## **7. Statistical analysis**

The following is an overview of the statistical considerations. Details of the pre-specified statistical analyses can be found in Statistical Analysis Plan (SAP).

Statistical analysis will be performed by independent analysts by using R (version 4.1.0; R Development Core Team) software. All the analyses will be based on an intention-to-treat principle. Continuous data will be represented by the average, standard deviation, median, minimum and maximum value; categorical data will be represented by the number and percentages. Continuous data will be analyzed using the t test or one-way ANOVA; Wilcoxon-Mann-Whitney test will be used when necessary. Categorical data will be analyzed using the chisquare test or Fisher's exact test. The logistic regression model or linear regression model and linear mixed model will also be used to find the relationship between independent variables. The subgroup relative risk (RR) and the corresponding 95% confidence intervals (CIs) are calculated together with interaction P values.  $P < 0.05$  will be considered statistically significant.

## **8. Privacy**

If the subject decides to participate in this study, the data of the subject recorded throughout the study are only used for scientific research purpose and not for any news or commercial ones. The personal data of the subjects involved will be kept strictly confidential. When the study are published, none of the personal privacy such as the name and contact information of the subjects will be identified. After the study is published, all the study materials will be preserved in Women's Hospital School of Medicine, Zhejiang University for verification of study implementation required by national regulatory authorities, scientific research management authorities and Ethics Committee.

## **9. Funding**

This study is supported by Association for Maternal and Child Health, Zhejiang Province, China

(ZY2020-01). The funder is responsible for the administrative and financial management of the study, and not involved in the design of the study, nor in the collection, analysis, and interpretation of data or in writing the manuscript.

## 11. Update on the Published Protocol

As compared to the published protocol ([name], [name], Chang Liu, Nicola Robinson, Myeong Soo Lee, Xiaoyang Mio Hu, Hye Won Lee, Rong Zhang, [name]\*. Effectiveness of acupoint hot compress on early puerperal rehabilitation of parturients after natural childbirth: study protocol for a prospective, multi-center, randomized controlled clinical trial. *Clinical and Experimental Obstetrics & Gynecology*.2021;48(6):1350-1357), the present study protocol has made several amendments.

- (1) The medical provision of two centers changed, which has limited the number of the available participants with inclusion criteria of the study, and these two centers were not included in the trial.
- (2) The analysis used in the present trial is referred to as an “per protocol” analysis.
- (3) To detect the effects of acupoint hot compress on reducing the incidence of urinary retention more accurately, we used a broader standard to identify postpartum urinary retention.
- (4) To detect the effects of acupoint hot compress on lactation, we used a detailed measurement to quantify the breastfeeding milk volume.
- (5) As all the outcomes collected from 6±0.5 hours to 76±0.5 hours after delivery, the changes of maternal weight is tiny, so the weight was not included in the analysis.

**Effects of acupoint hot compress during early puerperium on parturients after a vaginal delivery: study protocol for a randomized clinical trial**

## **1. Study Populations**

All subjects with randomization will be included in the analysis set regardless of whether they receive any treatment. According to the intention-to-treat principle, all analysis will be based on the randomization set.

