### **2.3.5.4 Subject drop-out and discontinuation**

- (1) Implementation of rescue due to postpartum hemorrhage, eclampsia, or other obstetric conditions;
- (2) Change of vaginal delivery to cesarean section;
- (3) Infection during delivery;
- (4) Indwelling catheter and the need to use diuretics due to disease within 6 hours after delivery;
- (5) Degree III laceration above the perineal fissure;
- (6) Neonatal transfer after birth;
- (7) The investigator can terminate the subject from continuing the clinical trial at any stage, if the investigator deems that the risks of continuing the clinical trial outweigh the benefits;
- (8) Subject's poor compliance to this trial.

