## 8. Safety Analysis

Adverse event listings will be generated and events will be classified according to seriousness, treatment relationship and resolution. Descriptive statistics (numerical measures, frequency tables) will be used to summarize the occurrence of adverse events and serious adverse events by intervention group.

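### SAP section 1 puts the safety tables on all randomised women, so women who never wore a compress dilute the device-related adverse-event rate, and the start of adverse-event counting is not defined

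*Supplement*

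**What the plan says.** SAP section 1 (Study Populations) defines one analysis set: "All subjects with randomization will be included in the analysis set regardless of whether they receive any treatment". It adds, under the intention-to-treat principle, that "all analysis will be based on the randomization set". Safety is not excepted.

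SAP section 8 (Safety Analysis) plans listings and descriptive statistics to "summarize the occurrence of adverse events and serious adverse events by intervention group". It also says that "events will be classified according to seriousness, treatment relationship and resolution". It names no safety set, no rule for grouping by care received, and no time from which events count.

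Protocol section 2.9 says that "AEs will be monitored and recorded in detail throughout the whole study period", without saying when that period starts or ends.

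On timing, Figure 1 (protocol section 2.3.3) has an axis counted from delivery. It puts randomisation at −t1, allocation at 0 and the first intervention at t1, within 30 minutes after delivery. Section 2.6.2 gives the same time for Intervention I. Section 2.3.5.4 lists "Change of vaginal delivery to cesarean section" among the reasons for drop-out, along with infection during delivery.

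**The concern.** Keeping every randomised woman is right for the efficacy comparison. It does not suit a harm that can occur only while a device is worn. A woman assigned to the compress who never receives one cannot have a device-caused event, yet under SAP section 1 she counts in the denominator. The reported rate then answers how often women assigned to the compress were harmed by it, not how often women who wore it were harmed. For a heat device applied for 4 hours at a time, readers will want the second figure.

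The undefined counting window is a separate weakness. If events in labour are recorded as adverse events, they enter the tables of both arms although no compress has yet been applied. That noise makes the arms look more alike in relative terms.

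**Working it through.** The documents give no adverse-event rate, safety denominator or never-exposed share, so there is no planned safety figure to reproduce. The event rates below are assumptions for illustration.

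**Inputs**
- Planned arm size: 600 (protocol section 2.4).
- Never-exposed share of the intervention arm, f: not given. Assumed 5%, 10% and 20%. The 20% is the drop-out allowance in section 2.4, which covers all causes; the lower values have no source.
- Device-related rate in exposed women, p: assumed 2.0%.

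**Step 1: can a randomised woman go unexposed?** Figure 1 places randomisation before time 0 and the first compress after delivery. Conversion to caesarean can be a reason to leave the trial only if women have entered it before delivery. So yes, although no section gives the time of randomisation relative to labour.

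**Step 2: denominator.** Device-caused events arise only in exposed women, so

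reported rate = p × 600(1 − f) / 600 = p(1 − f).

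| f | Exposed women | Expected events at p = 2.0% | Rate reported on 600 |
|---|---|---|---|
| 5% | 570 | 11.4 | 1.90% |
| 10% | 540 | 10.8 | 1.80% |
| 20% | 480 | 9.6 | 1.60% |

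The arm size cancels, so the relative fall is f whatever number is enrolled.

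**Step 3: counting window.** Now let 2% and 1% be the all-cause event rates after the matching start time, in compressed women and in controls. Let b be a rate of earlier labour events common to both arms. With f = 0:

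| b | Intervention | Control | Risk difference | Risk ratio |
|---|---|---|---|---|
| 0% | 2% | 1% | 1 point | 2.00 |
| 1% | 3% | 2% | 1 point | 1.50 |
| 5% | 7% | 6% | 1 point | 1.17 |

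Labour events raise both crude rates, leave the difference alone and shrink the ratio.

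**Step 4: both together.** With f = 10%, and uncompressed women at the 1% background rate, the crude intervention-arm rate is b + 0.9 × 2% + 0.1 × 1%. That is 1.9% at b = 0, 2.9% at b = 1% and 6.9% at b = 5%, against 2.0% in exposed women. The crude rate is too low only while b is below f × (2% − 1%), here 0.1 percentage point.

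**The case against.** **The plan already separates events by cause.** SAP section 8 classifies events by relationship to treatment, so a labour complication can be marked unrelated. This stands in part. It helps with the numerator, but it rests on judgement in an open-label trial, and it does nothing for the denominator.

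**Labour events may never be logged as adverse events.** Sections 2.3.3 and 2.7 record delivery information, including perineal condition, assisted delivery and curettage, as baseline data. This stands: their entry into the safety tables is an inference from an undefined window, not something the plan states.

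**The never-exposed share may be small.** Several reasons in section 2.3.5.4 can arise after the first compress: catheter or diuretic use within 6 hours, neonatal transfer, investigator termination, poor compliance. Such women would be exposed. Nor does any section say that a severe laceration prevents the first compress. Only caesarean conversion points plainly to non-exposure, and its frequency is not given. This stands, and it is why 20% is an extreme ceiling, not an estimate.

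**Stronger readings that the documents do not support.** A reader might infer that labour events also cause the harm rate to be understated. They do the opposite to the crude rate. A reader might infer that a difference between arms would be hidden. Labour events common to both arms leave the risk difference unchanged, and SAP section 8 plans no between-arm safety test or ratio. A reader might infer that an upper confidence limit for harm will be too low. No such limit is planned.

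**Conclusion.** The point holds for the denominator. As written, SAP section 1 governs the safety tables, and any never-exposed woman in the intervention arm lowers the device-related rate by the factor (1 − f). The direction is certain once f is above zero, given that device-caused events occur only in women who wore the device. The size cannot be derived from the documents: the illustration of 1.9% to 1.6% for a true 2.0% rests on an assumed f of 5% to 20%, and the real effect may be smaller.

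The missing counting start is a second, separate gap. Its effect, if labour events are logged at all, is on the relative contrast. The net direction of the crude all-cause rate cannot be stated, because it depends on both f and b.

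The primary efficacy analysis is untouched. This is a change the SAP should make, modest in size and standard in kind.

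**What to change.** Limit the all-randomised sentence in SAP section 1 to efficacy. For SAP section 8:

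- Define a safety set: intervention-arm women who received at least one compress, and control-arm women who delivered vaginally and began routine postpartum care. Women stay in it whatever happens later.
- List intervention-arm women with no compress separately. Do not move them to the control group.
- Count events from the start of the first compress, and in controls from the matching time after delivery. List earlier events separately.
- Report the number exposed at each of Interventions I, II and III.
- Keep the all-randomised adverse-event table as a supplement.

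Also reconcile item 2 of protocol section 11, which calls the analysis per protocol, with protocol section 7 and SAP section 1, which follow intention to treat. Until that is settled, the set that will actually be used is unclear.

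The cost is some SAP wording, one further denominator and a date filter. There are two downsides. The safety set is chosen after randomisation, so it is not strictly the randomised comparison; the supplementary table covers this. And compress start times and event onset times must be available from the case report forms. The documents do not say that they are captured, so this needs checking first.
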